**Grocery Store Receipts:** Participants in the diet arm will be asked to bring in all grocery store receipts for a 1-week period at baseline and 6 months to see what foods they are purchasing.

**Questionnaires:** Questionnaires will be completed to measure a variety of health-related variables as summarized in the Table below. A short battery of cognitive tests including for memory, attention and other related measures will be administered using standardized tests that are adapted for computer based testing by [name] (Director of Nutritional Neuroscinece) at Beth Israel Deaconess Medical Center and Harvard Medical School, Boston, MA. A follow-up questionnaire will be distributed either in person, online or over the phone at months 12 and 18 to capture changes in medication, specifically for diabetes, blood pressure and cholesterol.

**Recruitment Day(s):** Recruitment Day will be used as an opportunity to encourage employee participation in the study among the twelve worksites that have been selected for the Weight Loss or Human Performance Institute interventions. We will work with HR to conduct Recruitment Days for each of the twelve worksites. We will hold additional Recruitment Day sessions on an as needed basis, or if the worksites feel that this would increase participation. This will be determined on an individual worksite basis. Brief informational sessions for all employees will also be held at the beginning of each Recruitment Day. Study staff will also be available, in-person, to answer specific questions regarding participation. In addition to using Recruitment Day as an opportunity to disseminate informational flyers and brochures explaining the mission of our intervention programs, both height and weight measurements will be obtained from those who sign up for the study. This form has identifiers because the use of electronic de-identified data forms is not feasible. As participants move through the various measurement stations before their eligibility is verified. Please see confidentiality section for how these forms will be stored and handled. For employees wishing to enroll in the wellness intervention programs, height and weight measurements obtained on Recruitment Day will be used to confirm eligibility based on the stated inclusion/exclusion criteria.

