         3. Willingness to provide release from his/her physician before starting the intervention program-a requirement for each of the 3 wellness programs which can be faxed to [name], or emailed to [[contact]](mailto:[contact]) or mailed back to the HNRCA at [name].
         4. Willingness to provide email ID and contact information to the commercial program facilitators to receive program materials and other feedback related to program progress.
         5. Willingness to complete outcome assessments and self-monitoring in order to track intervention effectiveness
         6. BMI ≥ 20 kg/m^2^ and < 50 kg/m^2^ at screening, if participant opts into the HPI arm
         7. BMI ≥ 25 kg/m^2^ and < 50 kg/m^2^ at screening, if participant opts into the weight loss arm
      2. Exclusion criteria:
         1. Employees who are temporary contract workers or employees who work remotely most of the time
         2. < 21 years of age
         3. Participation in a weight loss program or intensive wellbeing program at time of enrollment
         4. Pregnant or lactating (per self-reports, now or intended during study)
         5. Prior weight loss surgery or a medical complication that would prevent full participation
         6. Multiple severe dietary intolerances (e.g. gluten combined with dairy or meat) which would reduce intervention adherence
         7. Non-English speaking
         8. Individuals who have lost > 15 pounds in the past 6 months
         9. mobility limitations (inhibiting the ability to stand on one’s own or get on and off of the scale)
         10. Major diseases including active cancer or cardiovascular disease
         11. BMI < 25 kg/m^2^ or ≥ 50 kg/m^2^ at screening, for those that opt-in to the weight-loss group
         12. BMI <20 kg/m^2^ or ≥ 50 kg/m^2^ at screening, for those that opt-in to the HPI group

For those interested in the weight loss intervention, additional exclusion criteria are as follows:

1. Any condition that influences the ability to absorb food (e.g. inflammatory bowel disease or celiac disease)
2. Very active individuals (> 2 hours/day or >14 hours/week of vigorous activity).

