We would like to note that there will be no exclusion of participants based on out of range blood values since the physician’s clearance form will serve as the reference document for inclusion in the study. Extreme values will be flagged and per the study physician’s recommendation participants will be sent a notification to see their primary care provider.

Non – English speaking participants will be excluded from participation as the proposed intervention programs and program related materials have yet to be translated into other languages and have yet to be designed or tested for non – English speaking populations. Furthermore we anticipate that since this is a worksite study most if not all employees will be English speaking

- - 1. Withdraw/Termination criteria: Participants will be withdrawn if they develop a condition that renders them ineligible after they sign consent including the period during which they are actively participating in the study. This includes women who self-report pregnancy, those whose health status changes affecting adherence to the diet, safety concerns for either the participant or the researchers, or outcome assessments (questionnaires) reveal that they have an exclusion criterion that they did not disclose at screening. Participants will be withdrawn from the study if they enroll in any other weight loss/intensive wellness program during the 18 month intervention. Furthermore the PIs with the consultation of the study physician may terminate or temporarily withdraw participants at their discretion if they feel that participant safety is of concern.

Participants may withdraw at any time for any reason. If participants decide that they wish to withdraw they will be provided a prorated stipend based on completion of study outcomes for the time point at which they withdraw and provided a stipend is identified at that time point.

If participants are deemed ineligible or withdraw at any time for any reason, any data collected up until this point in time will be retained throughout the duration of the study. We plan to discard this data 10 years after study completion. Retaining this data is necessary to report CONSORT chart details in any study publication(s).

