**Intervention goals and details for HPI and the iDiet**

| iDiet (iDiet) | |
| --- | --- |
| Primary goals | - *Goals*: Weight loss (1-2 lb/week), dietary energy reduction (**approximately** 500-1000 kcal/week) consumed in regular meals, encourage activity (150 minutes/week). Please note individualized calorie goals are used per program specifications, ranging from 1000 to 2500 calories depending on the weight of the participant. The minimum calorie target recommended for our smallest people will be 1000 calories/day, which may not be as great as a 500 calorie deficit, and participants are able to request a different menu level if they wish. The goal for physical activity is also a broad goal. Participants will be provided with pedometers and forms for tracking pedometer counts and other activities. If participants tracked activity levels do not meet program goals, counselors will suggest incremental strategies to increase activity weekly through brisk walking, lifestyle activities or other exercise of the participant’s choice. Physical activity will be recommended starting after Session 3 and will be emphasized as an important factor for preventing weight regain once subjects are in maintenance. Participants will not be excluded or withdrawn from the study if they do not meet this recommendation. - *Core strategies*: Group classes, behavioral skills training and materials (e.g. pedometer, family-friendly menu examples and a log for self-monitoring weight) to support study adherance. |
| Nutrition goals and strategies | - *Goals*: High fiber (>40 g/d), moderately high protein (26% energy), low glycemic load (48% energy with low GI carbs) - *Core strategies*: Use of provided calorie- and nutrient-controlled menus and recipes. General portion guidelines and self-monitoring for portion sizes |
| Behavioral goals and strategies | - *Goals*: Hunger supression and maintenance of satiety; changing food preferences - *Core strategies*: Adherence to specific, repetitive provided menus and cognitive restructuring exercises. Frequent meals, use of free foods, optional portion size monitoring; raising self-efficacy, exercise |

| Human Performance Institute (HPI) | |
| --- | --- |

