Those interested in participating will be screened on **Recruitment** Day. They will first be administered the screening ICF, and the screening will involve a questionnaire on exclusions and measurements of weight and height for calculation of BMI and the option to choose the diet or the HPI arm of the intervention. If the individual is eligible they will then be administered with the informed consent form (ICF) for baseline assessments. The **Recruitment** Days, screening and baseline measurements will be conducted by members of the Tufts team (study coordinators, research staff and investigators) depending on availability.

Randomization of worksites to the intervention or control condition will be done following the completion of baseline assessments. Once worksites are randomized to receive the intervention or weight-listed control condition, participants within the intervention worksite will be assigned to the intervention arm that they opted into at screening i.e. HPI or diet arm. However, those who had expressed an interest in the

iDiet will be further randomized to receive Yevo foods or a gift card. Once randomization has occurred, participants will be given the consent form to read and sign prior to enrollment in the study.

Any questions or concerns will be addressed by a study team member prior to signing of the ICF. Copies of the signed ICF will be given to the study participants. Enrollment of all participating sites and employees will occur over a 6 month period during the first year.

1. **Transportation:** No transportation will be provided for this study since all support and assessments are provided and conducted in the workplace.
2. **Informed consent process:** Eligibility for inclusion of a worksite is multistep and is summarized in the protocol (Section III, parts C and D).
   - 1. Informed Consent for Initial Web Survey For All Employees at Worksite
     2. HR Company Agreement Form
     3. Informed Consent for Worksite **Recruitment** Day and Screening
     4. Informed Consent for Baseline Assessments For All Employees who have expressed an interest to join an intervention group at Worksite
     5. Informed Consent for:
3. iDiet Intervention
4. Human Performance Institute Intervention
5. Control group

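### The withdrawal rule ends follow-up for events after randomisation, one of which can arise only on the diet, and so conflicts with the planned Intention-To-Treat analysis

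*Protocol*

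**What the plan says.** Under Subject Characteristics, the Withdraw/Termination criteria begin: "Participants will be withdrawn if they develop a condition that renders them ineligible after they sign consent". The sentence goes on to cover the time when people are actively taking part. The grounds it names are:

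- self-reported pregnancy;
- "those whose health status changes affecting adherence to the diet";
- safety concerns;
- outcome questionnaires that "reveal that they have an exclusion criterion that they did not disclose at screening".

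A further sentence withdraws from the study anyone who joins another weight-loss or intensive wellness programme during the 18 months.

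For people found ineligible or withdrawn, the same section keeps the data gathered up to then and gives CONSORT reporting as the reason. It makes no provision for measuring them afterwards.

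Sample size and statistical analyses commits both the HPI and the iDiet analyses to Intention-To-Treat, so that results reflect what follows when people start a programme. Multiple imputation is to be used if necessary.

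**The concern.** An Intention-To-Treat comparison needs outcomes on everyone randomised, whatever happens to their participation in the programme. Here a fixed protocol rule stops outcome collection because of events after randomisation. Two features make this more than ordinary dropout:

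- **The rule is not symmetrical.** A health change can affect adherence to the diet only in someone who is on the diet.
- **The grounds may be related to outcome.** A health change that disturbs dieting may also change weight and vitality. A person who joins another programme may be dissatisfied with progress or tired of waiting.

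At stake are the two primary outcomes: weight for iDiet, and SF-36 vitality for HPI against controls. This is a question of which data are collected. An analysis plan cannot recover measurements that the protocol told staff not to take.

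**Working it through.** The documents state no figure for withdrawals, so the check sets the sections side by side.

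**1. Timing.** Screening Interview/Questionnaire places worksite randomisation after baseline assessments. Withdrawals between consent and randomisation do no harm to the comparison. The rule also runs on through active participation, so it covers events after randomisation.

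**2. Which ground can act in which arm during the first 6 months.** Experimental design gives controls outcome assessments only in this period.

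| Ground | iDiet | HPI | Control |
|---|---|---|---|
| Health change affecting adherence to the diet | yes | no | no |
| Undisclosed exclusion found in questionnaires | yes | yes | yes |
| Joining another programme | yes | yes | yes |

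The first row can distort iDiet against control. In food against gift card, both groups are on the diet, so that comparison is distorted only if the frequency or outcome of such withdrawals differs between the groups. The vitality comparison of HPI with control is exposed through the other two rows. Joining another programme could well differ by arm, since controls are waiting for one, but the documents give no rates.

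**3. Effect on an estimate.** Let a proportion p of an arm be withdrawn, with mean outcome m_w had they been measured, and let m_k be the mean of those kept. The full-arm mean is (1 − p)·m_k + p·m_w. Using only those kept therefore shifts the arm mean by

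m_k − [(1 − p)·m_k + p·m_w] = p·(m_k − m_w).

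The bias in a two-arm difference is p₁·(m_k1 − m_w1) − p₀·(m_k0 − m_w0). For the diet-adherence ground against controls p₀ = 0, so nothing on the control side offsets the first term. The protocol gives neither p nor m_k − m_w, so no size can be calculated.

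**4. What is already scheduled.** Tables 1 and 2 (headed in weeks, though the text speaks of months) list these times:

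- Weight: 0, 3, 6, 9, 12, 15 and 18 at intervention sites; 0, 3 and 6 at control sites.
- SF-36: 0, 3, 6, 12 and 18 at intervention sites; 0, 3 and 6 at control sites.

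Continued follow-up needs no new visit.

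**5. Does the rule also remove people who lose the intended weight?** The iDiet goal is "Weight loss (1-2 lb/week), dietary energy reduction" and so on, and the active phase lasts 24 weeks. That gives 24 × 1 = 24 lb to 24 × 2 = 48 lb, with 15 lb reached at 15/2 = 7.5 to 15/1 = 15 weeks. The exclusion "Individuals who have lost > 15 pounds in the past 6 months" has no time anchor, unlike "BMI < 25 kg/m^2^ or ≥ 50 kg/m^2^ at screening, for those that opt-in to the weight-loss group". Other text settles the matter:

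- At screening, "the screening will involve a questionnaire on exclusions and measurements of weight and height for calculation of BMI", so the past 6 months look back from that day.
- Intended weight loss is not among the named withdrawal grounds.
- The data and safety monitoring section has its own rule for weight loss on study: quarterly physician review, case-by-case assessment of symptoms or concerns, and exclusion of those below BMI 21.0 who do not comply with advice to stop losing.
- iDiet entrants have BMI of at least 25, so falling below 21.0 means losing more than 4 BMI units. Since 15 lb is 6.80 kg and 6.80/4 = 1.70 m², whose square root is about 1.30 m, this exceeds 15 lb for anyone taller than about 1.30 m. The monitoring rule thus contemplates people still in the trial after losing more than 15 lb.

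**The case against.** **Imputation.** The strongest reply is that Intention-To-Treat is an analysis commitment: withdrawn people stay in the analysis set, their earlier data are kept, and imputation handles the rest. Part of this stands. Earlier weights do carry information, and the loss is smaller than if whole records were deleted. But imputation is planned only if necessary. A model fitted mainly to people still on the programme would tend to impute values as if the withdrawn person had continued, which is not the question the protocol says it wants answered.

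**Literal text.** The protocol nowhere says in so many words that measurement stops at withdrawal. That is fair. Yet it retains only what was gathered before and provides for nothing after, so staff would reasonably stop.

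**Narrow grounds.** Most grounds apply in every arm, and the diet ground requires a health change. This also stands. A reader might infer that poor adherers in general are removed; the text does not say that. Questionnaires follow the same schedule in both conditions up to month 6, so the undisclosed-exclusion ground is the least likely to be uneven there.

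**A stronger reading.** Because the 15 lb exclusion lacks a time anchor, a reader might infer that successful iDiet participants must be withdrawn and that the weight outcome is cut off in the best responders. Step 5 of the working shows why the documents do not support this. The vigorous-activity exclusion (above 14 hours a week) also lacks an anchor, but the programme's activity goal is 150 minutes a week, so no effect is apparent.

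**Conclusion.** The concern holds for the withdrawal rule itself. The protocol ends follow-up for events after randomisation, at least one of which can arise only in iDiet participants during the controlled 6 months, and this conflicts with its own Intention-To-Treat commitment. Bias in the weight and vitality comparisons is possible. Its size cannot be derived from the documents, and its direction depends on who is withdrawn. The conclusion rests on reading withdrawal as the end of outcome assessment, which is the natural sense of the section, and on the grounds being related to outcome, which is plausible but not shown. It does not extend to participants who lose more than 15 lb: the documents do not call for their withdrawal, and no estimate built on that reading should be used.

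**What to change.** Amend the Withdraw/Termination criteria to distinguish two things: stopping the intervention and leaving the study. Who stops a programme, and when, can stay as a clinical decision and needs no change for this purpose. For every randomised participant in every arm, state that the scheduled weight and SF-36 assessments continue after the programme stops, after an undisclosed exclusion is found, or after another programme is joined. The exceptions are withdrawal of consent and cases where a measurement is not appropriate. State that these participants are analysed as randomised, and record the date and reason for stopping so that sensitivity analyses are possible.

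As a wording clarification only, add that the 15 lb and vigorous-activity exclusions apply at screening, as the BMI limits already do.

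The cost is a protocol amendment and a check that the consent forms cover continued assessment. No visit is added, though a few more people must be kept in contact. The small downside is that some participants no longer on the programme are measured, which may make the estimated effect slightly less favourable. That is the effect an Intention-To-Treat analysis is meant to report.

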2. **Experimental design:** 18-month worksite randomized controlled trial, in which worksites are randomized to receive the multiple intervention wellness programs or the control program. Control participants will participate in outcomes assessments only for the first 6 months, after which they will enroll in the intervention of their choosing. Both arms (HPI and the iDiet) will receive direct training from the coaches who deliver these commercial programs at their respective worksite and/or via a concurrent online session, or at an alternative commutable location that is offsite in the case of the HPI program. A total of 400 participants in the worksites allocated to the intervention, with approximately 20 participants in the HPI arm and 30 in the iDiet arm per worksite is planned to ensure even balance in each of the study arms. If more than 20 individuals are interested in and eligible for the HPI arm or more than 30 are interested in and eligible for the diet arm, participants will be enrolled into the study on a first-come, first-serve basis, including a small upward or downward adjustment in the total number of employees enrolled per site to ensure that the overall targeted number of participants is achieved. All participating individuals, from both the intervention wellness and control programs, can opt-in to either the HPI or the iDiet weight loss program. However, if they choose to participate in the weight loss intervention they will then be randomized into one of two groups: iDiet with food provided or iDiet with a gift card,. The study flow and primary intervention groups are described below:

**
[figure not shown]
**

*^1^The number of controls reflects study design in which sign up for the intervention and distribution of the intervention sites happens before baseline to ensure equivocal disposition*.

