- In addition as stated in the company agreement, “in the event of low employee participation (less than 50 individuals joining the interventions), Tufts may decide to exclude Company Name from the study” any eligible worksite that enrolls may be withdrawn by the Principal Investigator (s).

1. **Risk/benefit assessment:** This is a randomized controlled study that has minimal risk associated with the research activities for worksite participants.

The major potential risk associated with the study is considered to be breach of confidentiality. To address this, upon entry into the study, a coded study ID will be assigned to the study subject and biological materials and questionnaires to maintain confidentiality within the research setting. The signed consent forms data on paper forms will be kept in a locked file cabinet in the USDA Human Nutrition Research Center. Only the principal investigators and Study Coordinator will have access to the master code linking subject identifiers and their study ID. All investigators at Tufts undergo the required continuing recertification for ethical research by human subjects. Study investigators will see only de-identified data. The reviewing IRB is authorized to see fully identifiable data. Computer files and data collection forms will use the subject ID and will not be linked to protected information. The computers used to enter or store study data will be password protected. All data will be entered into StudyTRAX. Security features of StudyTRAX targets include password protection, restricted access to users based on role in the study, role-based access to features, access audit trails, and hosting services (e.g., firewall, secure sockets layer). Taken together, these features ensure access control, audit control, data integrity, user authentication, and transmission security. The research project will be set up in StudyTRAX using their standard procedure which ensures exported datasets are de-identified as defined in the HIPAA privacy regulation [45 C.F.R. §164.514 (b)(2)]. However, there is always the risk that confidentiality may be lost due to reasons beyond the control of study staff.

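### Mandatory study withdrawal on joining another programme ends outcome collection against the ITT aim, and the 50-person worksite exclusion is not confined to the time before randomisation

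*Protocol*

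**What the plan says.** Both rules stand under Withdraw/Termination criteria in the Subject Characteristics section of the protocol.

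- **Participants.** "Participants will be withdrawn from the study if they enroll in any other weight loss/intensive wellness program during the 18 month intervention". For anyone who is withdrawn, "any data collected up until this point in time will be retained throughout the duration of the study"; the reason given is the participant flow chart for publications. Nothing says that outcome assessment continues after withdrawal.
- **Worksites.** The protocol cites its agreement with each company: "in the event of low employee participation (less than 50 individuals joining the interventions), Tufts may decide to exclude Company Name from the study". It extends this to every eligible worksite that has enrolled and leaves the decision to the principal investigators. It does not say when the count is taken.

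The section on sample size and statistical analyses commits both studies to intention-to-treat, with multiple imputation if needed. The experimental design plans for "approximately 20 participants in the HPI arm and 30 in the iDiet arm per worksite" and allows site totals to be adjusted slightly up or down.

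**The concern.** Joining an outside programme happens after randomisation and is unlikely to be unrelated to what the trial measures. A wait-listed control may look for help elsewhere, and so may an intervention participant who is not benefiting. Such people leave the study, not only the programme, so the 6-, 12- or 18-month values still due are never collected. Intention-to-treat needs those values. An analysis plan can define who is analysed, but it cannot recover measurements that the protocol stops taking. Multiple imputation would have to predict the outcomes of people who switched from people who did not.

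The worksite rule raises a separate question. With 12 randomised units, a discretionary exclusion that can be used after allocation is known would weaken the randomised comparison and cost power.

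**Working it through.** **1. Participant rule.** The rule is mandatory and covers the full 18 months. The Outcomes section sets the weight outcome at 18 months and the comparison of energy status with controls at 6 months. A participant who joins another programme in, say, month 4 has a baseline value and perhaps a 3-month value, but no later one. The text provides for no post-event measurement. The protocol gives no expected frequency of such events, so the amount of missing data cannot be calculated.

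**2. Timing of the worksite rule.** Three statements in the Screening Interview/Questionnaire section matter:

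- "Randomization of worksites to the intervention or control condition will be done following the completion of baseline assessments"
- "participants within the intervention worksite will be assigned to the intervention arm that they opted into at screening"
- "Once randomization has occurred, participants will be given the consent form to read and sign prior to enrollment in the study"

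Programme choice and baseline come before worksite randomisation, so a count of sign-ups could be settled beforehand. Consent to enrol comes after it, so a count of people who actually join can be completed once the arm is known. The rule does not say which count is meant. Nor does it say what joining means at a control site, where no programme starts for 6 months.

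**3. Threshold against planned site size.** The planned size is 20 + 30 = 50 per site; also 600/12 = 50 overall and 400/8 = 50 in the intervention arm. The threshold therefore has no margin, and a site adjusted down to 48, as the design section appears to allow, could be excluded. For illustration only, if site counts were Poisson with mean 50 (an assumption), about 48% of sites would fall below 50. At the enrolment ceiling of 700/12 = 58.3 per site, about 12% would.

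**4. Power for vitality.** The inputs come from the sample size section: within-site SD 15, 20 people per site, between-site SD at most 3.4, a 9-point difference, 8 intervention and 4 control sites, two-sided 0.05.

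- Variance of a site mean: 3.4² + 15²/20 = 11.56 + 11.25 = 22.81.
- SE = √(22.81 × (1/8 + 1/4)) = 2.925.
- Non-centrality = 9/2.925 = 3.077.
- Power from the non-central t with 8 + 4 − 2 = 10 df: **79.2%**. This reproduces the stated 80%.

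The same calculation with fewer sites, df being the number of sites minus 2:

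| Intervention : control sites | Non-centrality | Power |
|---|---|---|
| 8 : 4 | 3.077 | 79.2% |
| 7 : 4 | 3.007 | 76.3% |
| 6 : 4 | 2.919 | 72.5% |
| 8 : 3 | 2.784 | 69.8% |

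The reduced-site rows are illustrations; the protocol does not predict that any site will be lost.

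**The case against.** The worksite rule reads most naturally as a recruitment check. It comes from the company agreement, about 50 employees is already an expectation in the worksite eligibility list, and sign-up, screening and baseline all precede randomisation. It is also permissive, not automatic. A reader might infer that worksites are dropped after randomisation, for reasons tied to outcome, in the intervention arm only. The document does not say so. It gives no timing, it covers any enrolled worksite, control employees also choose a programme beforehand, and low enrolment is not an outcome. What stands is narrower: the text does not rule out use after allocation, and consent after randomisation leaves room for it.

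A reader might also infer that withdrawn participants are removed from the analysis. That is not stated either. Their earlier data are kept, intention-to-treat and imputation are foreseen, and the definition of analysis sets may sit in an analysis plan that is not at hand. This answers a charge of deletion. It does not answer the loss of follow-up, which the protocol itself causes.

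Finally, controls are promised a programme of their choice at 6 months, which gives them a reason to wait. How many would go elsewhere is unknown.

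**Conclusion.** The point holds in this limited form. The participant rule, followed as written, ends outcome collection after a post-randomisation event plausibly related to allocation or response, and so conflicts with the intention-to-treat aim. That the data would be missing not at random is a judgement about why people join other programmes; it is not a figure in the document.

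It is tempting to conclude that the rule biases the result in favour of the intervention by a known amount. The document supports neither a direction nor a size. In particular, a hypothetical shift in the control mean cannot be set against the 2.4% weight difference in the sample size section, because that figure is the contrast of provided food with gift cards among iDiet participants and contains no controls.

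For worksites, the defect is that the timing is not fixed and the threshold has no margin. On the protocol's own inputs, and with a t test on worksite means, losing one intervention site lowers power from 79.2% to 76.3%, and losing one control site lowers it to 69.8%.

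**What to change.** 1. In the withdrawal criteria, separate stopping a programme from leaving the study. Participants who join another programme keep attending the scheduled outcome assessments unless they withdraw consent. They are analysed as randomised, with the event and its date recorded.
2. State that the 50-person check applies only to sign-ups before worksite randomisation, and reconcile the threshold with the site-size adjustment allowed in the experimental design. State that every randomised worksite stays in the intention-to-treat analysis whatever its later uptake.

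Withdrawal for safety, pregnancy or other health reasons is outside this change and stays with the investigators.

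The cost is revised wording in the protocol and the company agreement, and a few extra assessments in people already enrolled.
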